## INTRODUCTION

1

Approximately one in four persons with cancer expresses symptoms of depression [1]. Individuals with cancer and depression are at high risk for severe disability, challenges in returning to work, high risk of suicide, lack of adherence to treatment, poorer prognosis, and decreased survival [2]. Additionally, depression increases the number of visits, hospital admissions, and medical costs [3]. Depression is specifically linked to cognitive deficits in memory, learning, attention, and concentration [4], as well as sleep disturbances, disability, difficulties at work, and suicide risk, all of which worsen the prognosis and increase the risk of relapses or chronicity [2, 5].

Among people with cancer, depression is particularly not recognized or treated. Only 10% of patients receive mental health care. In this sense, primary prevention is practically absent [6] due to the lack of effective screening tools and the poor structure of specialized medical education courses in the Italian and international contexts [7]. Developing personalized screening tools could improve the identification of high-risk patients and their enrolment in specialist treatment pathways at the second or third level [7, 8]. Despite its significant impact on individuals and healthcare systems, substantial gaps remain in the clinical and rehabilitative management of depression among people with cancer. There are no specific guidelines for psychotropic drug usage, and the efficacy of antidepressants is uncertain despite their frequent use [9].

Among non-pharmacological treatments, physical activity is recognized for its preventive and rehabilitative efficacy in addressing mental health complications, particularly concerning depressive and anxiety symptoms [10].

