discomfort, and anxiety/depression, with each rated on a three-level (EQ-5D-3L) or five-level (EQ-5D-5L) scale, indicating no problems to extreme problems. The VAS records the respondent's self-rated health on a scale from 0 (worst health imaginable) to 100 (best health imaginable). It demonstrates good internal consistency and reliability, with Cronbach's alpha values ranging from 0.6 to 0.85, varying based on the population and clinical context.The SF-12 Health Survey [28] is a brief version of the widely used SF-36, designed to measure health-related quality of life. It consists of 12 items that cover physical and mental health domains. The SF-12 assesses the impact of health on daily functioning, pain, energy, emotional well-being, and role limitations due to physical or emotional problems. It demonstrates good internal consistency and reliability, with Cronbach's alpha values typically exceeding 0.80 for both physical and mental health domains.

Both of the above questionnaires will be administered according to the following timeline: T0 (0 months-baseline), T1 (3 months-post-intervention), T2 (3 months after T1), and T3 (6 months after T1).

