
Toronto Alexithymia Scale 20-item (TAS-20) [43] is a self-report questionnaire designed to assess the degree of alexithymia. It consists of 20 items that measure three key dimensions of alexithymia: difficulty identifying feelings, difficulty describing feelings, and externally oriented thinking. The instrument demonstrates strong internal consistency, with Cronbach’s alpha ranging from 0.80 to 0.90. The questionnaire will be administered according to the following timeline: T0 (0 months-baseline), T1 (3 months-post-intervention), T2 (3 months after T1), and T3 (6 months after T1). A summary of the timeline is provided in Fig. (**1**).

The tertiary outcome will be measured as cost-effectiveness [3] of the nonpharmacological treatments (VR-COG and rTMS), and it will be computed as the ratio of total costs divided by the mean improvements of quality of life across interventions (TAU, TAU+rTMS, TAU+VRCOG). Total costs will include the costs of the healthcare consultations (visits in the TAU condition), psychotropic drugs, equipment, and staff. Total costs will be computed as the sum of the costs of each intervention, divided by the number of patients. Quality of life improvements will be computed as the difference between the baseline (T0) and the endpoint (T3) quality of life. A summary of the timeline is provided in Fig. (**1**).

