### Statistical Analysis

2.11

The baseline data will be summarised as percentage (absolute numbers) for qualitative variables and median (1^st^ and 3^rd^ quartiles) for continuous variables. The group sequential Bayesian design [49] will be used to analyze the study's primary endpoints. Additionally, the first interim analysis will be carried out when 70% of enrolment is reached. The pattern chosen for the evaluation of the risk ratios of the primary endpoint will be defined by a beta-binomial model [50]. Apart from that, a SHELF (Sheffield Elicitation Framework) elicitation paradigm [51] will be used to define the prior probability of remission in the three intervention groups. The elicitation procedure will be carried out using R Shelf software [52]. Non-informative priors will still be used for sensitivity analyses. Upon reaching the interim, the probability that the posterior RR (relative risk) estimates, for the TAU *versus* rTMS or TAU *versus* VR-COG comparison, imply a value greater than 1 and surpass an efficacy boundary established in the interim, will be calculated. If at least one posterior probability for comparison using informative and non-informative priors exceeds the interim boundaries, then the trial will end due to efficacy; otherwise, the trial will continue until the end of the study. If the trial advances, the posterior probabilities for the RRs, with 95% confidence intervals, will be calculated. The intervention will be considered effective if the posterior probability that the RR exceeds 1 is higher than the ultimate effectiveness boundary. Secondary analyses will be performed using generalized Bayesian models by taking into account the interventions as a covariate and reporting 95% posterior confidence intervals. The convergence of the models will be evaluated using trace plots and Gelman statistics. The data will be analysed with an intention-to-treat approach and imputation of missing data according to a Last Observation Carried Forward (LOCF) protocol [53].

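### The cost-effectiveness benefit is read at month 9 with LOCF and no exception for death, so a patient who dies is scored with the last quality of life measured while alive

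*Protocol article*

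**What the plan says.** Section 2.4 (Evaluation Tools and Evaluation Timeline) defines the tertiary outcome as a ratio: "it will be computed as the ratio of total costs divided by the mean improvements of quality of life across interventions". The denominator is a two-point change: "Quality of life improvements will be computed as the difference between the baseline (T0) and the endpoint (T3) quality of life". The quality-of-life questionnaires are given at T0, at T1 (month 3) and then at "T2 (3 months after T1), and T3 (6 months after T1"), which puts T3 at month 9. The numerator is a cost per patient: "Total costs will be computed as the sum of the costs of each intervention, divided by the number of patients".

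Section 2.11 (Statistical Analysis) gives the one rule for absent values: "The data will be analysed with an intention-to-treat approach and imputation of missing data according to a Last Observation Carried Forward (LOCF) protocol". It excepts no outcome and no reason for absence. Section 2.9.5 (Methods to Handle Missing Data) covers only efforts to limit missing data and to follow patients who withdraw early. No section gives death a value or treats it separately. The introduction lists, for people with cancer and depression, "poorer prognosis, and decreased survival".

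**The concern.** Intention-to-treat requires a T3 value for every randomised patient, and a patient who has died has none. The stated rule supplies the last score recorded while the patient was alive and treats it as the health state at month 9. Death is a known outcome, with the value 0 on a utility index. It is not an unobserved measurement. Carrying the last score forward removes the loss of health from the denominator of the ratio.

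At stake is the cost-effectiveness figure, which appears in the trial's title and which the article's conclusions say will inform policymakers. The denominator is a small mean change, and one arm has only 20 patients, so a single event can matter.

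**Working it through.** The article states no figure that could be reproduced here. It gives no mortality, utility, cost or dropout value. The check applies its own rule to labelled assumptions.

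**Inputs from the article**
- Arm sizes: 60 patients at 1:1:1 plus 40 at 1:1 gives TAU 20+20 = 40, VR-COG 20+20 = 40 and rTMS 20. This agrees with the 2:2:1 allocation in section 2.11.1.
- Benefit: mean of T3 minus T0. Absent T3: LOCF.

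**Assumed inputs (not in the article)**
- Last living utility u = 0.6-0.8.
- Mean gain g = 0.05-0.10.
- For the ratio, baseline utility u0 = 0.5-0.7 and a cost of 1,000 units per patient.
- 9-month mortality p = 1-3%.

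**Step 1. What the rule does to one patient.** Death after T1: the score at T1 or T2 is carried, so the patient keeps the change seen at that visit. Death before T1: T0 is carried, so the change is 0. With death valued at 0, the change is -u0 in both cases.

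**Step 2. Overstatement per death.** The arm's mean T3 value is too high by u/n.
- n=20: 0.6/20 = 0.03 to 0.8/20 = 0.04.
- n=40: 0.6/40 = 0.015 to 0.8/40 = 0.02.

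Relative to the assumed gain, that is 0.03/0.10 = 30% to 0.04/0.05 = 80% for n=20, and 0.015/0.10 = 15% to 0.02/0.05 = 40% for n=40.

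**Step 3. Effect on the ratio of one death after T1.** Take the patient's last change to equal the arm mean g and the cost to be unchanged. LOCF then gives mean gain g. Death at 0 gives ((n-1)g - u0)/n. For n=20, g=0.05, u0=0.5: (0.95 - 0.5)/20 = 0.0225, and 1,000/0.0225 = 44,444.

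| n | g (gain under LOCF) | Gain, death at 0 | Ratio, LOCF | Ratio, death at 0 |
|---|---|---|---|---|
| 20 | 0.10 | 0.06-0.07 | 10,000 | 14,286-16,667 |
| 20 | 0.05 | 0.0125-0.0225 | 20,000 | 44,444-80,000 |
| 40 | 0.10 | 0.08-0.085 | 10,000 | 11,765-12,500 |
| 40 | 0.05 | 0.03125-0.03625 | 20,000 | 27,586-32,000 |

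With two deaths among 20 patients and g=0.05, LOCF still reports a gain of 0.05. Death at 0 gives (18×0.05 - 2u0)/20 = -0.005 to -0.025, a loss.

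**Step 4. Death before T1.** For n=20 and g=0.10, LOCF gives 19×0.10/20 = 0.095. The mean gain does fall, but to 0.095 and not to the 0.06-0.07 that follows when death is valued at 0.

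**Step 5. How likely a death is.** The chance of at least one is 1-(1-p)^n. For the whole trial (n=100) it is 63% at p=1% and 95% at p=3%. For the rTMS arm (n=20) it is 18% and 46%. The expected number is 1-3 in the trial and 0.2-0.6 in the rTMS arm.

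**The case against.** The strongest reply is that the article never says a death counts as missing data, and that the handling of deaths in an economic analysis can be left to a full protocol or analysis plan that is not shown. A bare omission could be left there. But the article does fix both the T3 endpoint and LOCF for absent values without exception, and together these give a definite and wrong score for a death. A later document could correct that only by departing from the published rule.

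Several other objections stand and limit the point:
- **Few deaths are likely.** Section 2.2 requires non-advanced disease and a Karnofsky score above 80, and excludes suicidal ideation. At p=1% the rTMS arm has an 82% chance of no death.
- **The quality-of-life score is not fixed.** Section 2.4 lists the EQ-5D (descriptive part and visual analogue scale) and the SF-12, without saying which enters the ratio. A value of 0 for death belongs to the utility index.
- **The outcome is tertiary**, in a study that describes its evidence as exploratory.

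A reader might go further and infer that a patient's costs stop at death, so that mortality makes an arm look cheaper. The article does not support this. It lists cost items ("Total costs will include the costs of the healthcare consultations (visits in the TAU condition), psychotropic drugs, equipment, and staff") but gives no cost window, and the interventions end at month 3, so little of their cost is left to save after T1. Even if 10% of one patient's cost were avoided in an arm of 20 with g=0.10, the ratio would move only from 10,000 to 995/0.10 = 9,950; at 50% avoided, to 975/0.10 = 9,750.

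A reader might also infer that the remission endpoint is affected. That would need remission to be read after T1, and the article does not state the visit.

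**Conclusion.** The concern holds for the quality-of-life side of the ratio. As written, a death after T1 does not reduce the arm's mean gain, and a death before T1 is counted as no change. Each death overstates the arm's mean T3 utility by 0.03-0.04 (rTMS) or 0.015-0.02 (TAU or VR-COG), given last utilities of 0.6-0.8. Against a mean gain of 0.05-0.10 this is material, most of all in the 20-patient arm.

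Only the arm sizes and the scoring rule come from the article. The utilities, gains and mortality are assumptions. Few deaths are to be expected, and the ranking of arms would be distorted only if deaths fall unevenly, which nothing in the article predicts. It does not follow that mortality makes an arm cheaper, that every death leaves the mean gain untouched, or that the primary endpoint is biased.

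**What to change.** In sections 2.4 and 2.11, state that LOCF does not apply after death. In section 2.4, name the EQ-5D index as the quality-of-life measure for the cost-effectiveness ratio and set it to 0 at T3 for patients who have died by then. This fits the two-point difference the article already uses. Report deaths by arm beside the ratio.

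The cost is a sentence or two. The only extra information needed is whether each patient was alive at T3, which follow-up and adverse event reporting should already yield. The downside is that an arm with a death gets a less favourable figure and, in the rTMS arm, one event can move the ratio a good deal. Reporting the deaths lets the reader see that.

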### Setting

2.5

All the activities will be carried out in two facilities of the Italian National Health Service:

Interhospital Psycho-Oncology Program, Psychiatry Unit, Mental Health Department for Pathological Addictions, Health Trust Unit of Ferrara, Italy (unit 1).Center of Liaison Psychiatry and Psychosomatic Medicine and Medical Oncology Unit, University Hospital of Cagliari, Italy (unit 2).

### Randomization

2.6

As shown in Fig. (**2**), the randomization will be conducted at units 1 and 2 after baseline assessment. Randomization will be computer-based and concealed. The people who will conduct the randomization procedure will be blind to the participants’ identities and status and will not receive any information on the participants. Randomization will be performed by blocks of randomized permutations to experimental and control treatments at a 1:1:1 (unit 1) and 1:1 rate (unit 2). Codes will be masked.

### Allocation Concealment

2.7

At least three different professionals will be present in the two study units: coordinator, evaluator, and clinician. In addition, the study will require the presence of a single person (statistician) for the two units, who will be responsible for the randomization procedures. Recruitment will be done by the study clinician or the clinical facility members, where the screening procedures will be carried out (medical oncologist, psychologist, or psychiatrist). They will propose participation in the trial to interested patients and will obtain their informed consent. Then, the clinicians will perform an initial screening of the inclusion/exclusion criteria and will get in touch with the coordinator if the eligibility requirements are satisfied. They will then reach out to the study's evaluator, who will then perform the baseline assessment. The statistician will perform the randomization procedure after receiving the data required from the coordinator. To ensure individual blinding of the clinical assessments by the evaluator, the randomization list will be shared with the coordinator and the clinician but not with the evaluator.

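### The randomization list goes to the recruiting clinician and the coordinator with no limit on timing or content, which conflicts with the concealment claimed in Section 2.6

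*Protocol article*

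**What the plan says.** Section 2.7 sets out the path into the trial. "Recruitment will be done by the study clinician or the clinical facility members", and these staff also obtain consent. Next, "the clinicians will perform an initial screening of the inclusion/exclusion criteria" and contact the coordinator when the criteria are met. The evaluator carries out the baseline assessment. Then "The statistician will perform the randomization procedure after receiving the data required from the coordinator".

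The section closes with its only rule on access to the list. The stated purpose is "To ensure individual blinding of the clinical assessments by the evaluator", and the rule is that "the randomization list will be shared with the coordinator and the clinician but not with the evaluator".

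Section 2.6 (Randomization) places randomization after the baseline assessment and uses permuted blocks, 1:1:1 in unit 1 and 1:1 in unit 2. It gives no block size. It states "Randomization will be computer-based and concealed" and "Codes will be masked", without saying from whom the codes are masked. It also says that those who run the randomization know nothing about the participants.

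Section 2.8 (Blinding) says that participants cannot be blinded and that the study is single-blind, with participants asked not to reveal their treatment to the evaluator. Section 2.10 (Ethical Issue) has the clinicians responsible for TAU collecting written consent.

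**The concern.** Allocation concealment and blinded assessment are separate safeguards. Concealment acts before enrolment: whoever decides that a patient enters, and when, must not know the next assignment. Blinded assessment acts afterwards, on the rating of outcomes. Section 2.7 carries the first name, but the rule it gives serves the second.

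The clinician who invites, consents and screens is named as a recipient of the list. A person who knows or can guess the next assignment can hold a patient back, bring one forward, or lean on an eligibility criterion that needs judgement. The pull is real in this design: each experimental arm adds 24 sessions over 12 weeks to TAU (Sections 2.9.2 and 2.9.3), so a recruiter may want motivated patients in those slots. Steering of that kind would distort the remission comparison and also drop-out, which is one of the feasibility measures under the primary outcomes. Intention-to-treat analysis and stratification by site (Sections 2.11 and 2.11.1) do not correct selection that happened before randomization. Adjustment for measured baseline prognosis, such as baseline HAM-D-17, could remove part of it but not the unmeasured part.

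**Working it through.** The point is procedural, and the protocol gives no figure for it. The check is therefore a comparison of roles, followed by two illustrations on stated assumptions.

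**1. Roles side by side (Sections 2.6 to 2.8)**

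| Role | Part in enrolment | Receives the list? |
|---|---|---|
| Study clinician | recruits, takes consent, screens | yes |
| Clinical facility members | may recruit and take consent | not named |
| Coordinator | receives eligible patients, sends the data that trigger randomization | yes |
| Evaluator | baseline and outcome assessment | no |
| Statistician | performs randomization | responsible for it |

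The only role barred from the list is the evaluator, who does not decide who enters. The clinician, who does, is given it. The rule does not limit sharing to assignments already made. Section 2.6 keeps the randomizer ignorant of the participants, but that does not keep the recruiter ignorant of the sequence.

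**2. If the full list is shared in advance.** The next assignment is known every time, and nothing is left of the concealment in Section 2.6.

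**3. If only past assignments are shared.** Suppose that the recruiter knows every earlier assignment at the site and knows a fixed block size, and guesses the arm with most places left in the block. The block sizes are assumptions. The share of correct guesses is the average, over positions in the block, of the probability of a correct guess:

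- two arms, block of 2: (1/2 + 1)/2 = 75%
- two arms, block of 4: (1/2 + 2/3 + 2/3 + 1)/4 = 71%
- two arms, blocks of 6 and 8 (simulated): 68% and 67%
- three arms, block of 3: (1/3 + 1/2 + 1)/3 = 61%
- three arms, blocks of 6 and 9 (simulated): 56% and 53%

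Chance is 50% with two arms and 33% with three.

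**4. What selection could do to the error rate.** Inputs from Section 2.11.1 are TAU remission 0.6, Beta(1,1) priors, boundaries 0.997 at interim and 0.976 at the end, and interim arms of 28 TAU, 28 VR-COG and 14 rTMS. The 2:2:1 ratio with 100 participants gives final arms of 40, 40 and 20. With x remissions among n patients, the posterior is Beta(1 + x, 1 + n − x). A comparison succeeds if P(RR > 1), that is P(experimental rate > TAU rate), exceeds the boundary at either look. Over 200,000 runs with no treatment effect, at least one comparison succeeded as follows:

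| TAU / experimental rate | Gap (assumed) | At least one false positive |
|---|---|---|
| 0.600 / 0.600 | none | 4.7% |
| 0.575 / 0.625 | 5 points | 11.1% |
| 0.550 / 0.650 | 10 points | 22.1% |

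The first row reproduces the plan's own claim of less than 5%. In the other two rows the gap is imposed, equally on both experimental arms. Nothing in the document ties access to the list to a gap of any size.

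**The case against.** The strongest reply concerns order and timing. Section 2.7 runs through recruitment, consent, screening and baseline, then has the statistician randomize on the coordinator's data, and only then mentions sharing. If the coordinator and clinician already held the sequence, that step would have little purpose. Section 2.6 also says that allocation is concealed and codes masked. A coherent reading is that assignments are passed on after randomization to those who must deliver treatment, and kept from the evaluator.

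Much of this stands. A reader might infer that upcoming assignments are handed to recruiters and that concealment is absent. The text does not say when the list is shared, so that cannot be stated as fact. A reader might also take the coordinator for a recruiter, or the trial for wholly unblinded. The coordinator neither recruits nor screens, and the evaluator is blinded. Facility members who recruit are not named as receiving the list. Nor are the 11% and 22% error rates predictions, since they follow entirely from assumed gaps.

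The reply does not clear the sentence. It says list, without limit, and its recipients include the person who recruits. Under the milder reading, a running record of permuted-block assignments in the recruiter's hands still makes the next one partly predictable. Some of that leak exists in any trial where treating staff recruit and see allocations, but the plan states no protection against it, and sharing the record makes it complete. Nor is this detail that an article may leave to a fuller protocol: the article states the rule, and the rule as worded conflicts with the section before it.

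**Conclusion.** The concern holds in a conditional form. That Sections 2.6 and 2.7 conflict as worded is firm: the access rule protects assessment, leaves enrolment unprotected, and names the recruiting clinician as a recipient. How far concealment is lost depends on a practice that the document does not describe. It is lost entirely if the full list is shared in advance. If only past assignments are shared, it is weakened, with correct guesses at 67–75% (two arms) or 53–61% (three arms) under assumed fixed and known block sizes. Participants are unblinded and the clinician knows the allocations, while the evaluator is blinded; that blinding does not prevent selection at entry. No size of bias can be derived from the document, and the simulated error rates show only that the plan's false-positive claim assumes comparable groups. The case for correction rests on the conflict and on the fact that selection at entry cannot be fully repaired afterwards.

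**What to change.** Amend the sentence in Section 2.7 rather than deleting it, because it is also the only statement that the list is kept from the evaluator. The new text should say that:

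- the full list and the block sizes stay with the statistician, or in a locked REDCap module;
- each single assignment is released to the coordinator and the treating clinician only after consent, confirmed eligibility and the baseline assessment are recorded for that study ID;
- block sizes are varied and withheld from both sites;
- the evaluator receives neither the list nor individual assignments.

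Section 2.6 should then say from whom the codes are masked, so that the two sections agree.

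The cost is a few sentences and a permission setting. The statistician's role already exists and REDCap is already the data system (Section 2.9.4). Sample size, arms and analysis do not change.
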